### Safety and adverse events

CBT is a clinically proven therapeutic intervention with no known associated risks. However, as one of the aims of CBT interventions is to promote independence, the participants will be instructed to increase their ADL, physical exercise, and social participation. Potential hazards will be discussed in the CBT sessions before these behavioral changes are effected. Information on safety precautions will be provided, and the participants will be aided in the development of strategies to minimize potential hazards and ensure safety. The therapists and research personnel will report any and all adverse events to the Departmental Research Committee of the Hong Kong Polytechnic University.

### Outcome measures

#### Primary outcome measure

##### Balance confidence

Our primary outcome of interest is FoF, which will be measured using the Chinese version of the Activities-specific Balance Confidence Scale (ABC) [34]. The ABC-C consists of 16 items representing specific situations in daily life rated on a scale from 0% (no confidence) to 100% (complete confidence). The ABC has been validated for use with community-dwelling elderly [42] and people with various medical conditions, such as Parkinson’s disease [43] and stroke [44, 45]. The ABC has also been translated into Chinese (Cantonese), and shows an excellent internal consistency (Cronbach’s alpha = .97) and a high test-retest reliability (intraclass correlation coefficient = .99) [34].

#### Secondary outcome measures

##### Fear-avoidance behavior

The participants’ engagement in fear-avoidance behavior will be assessed using the Chinese version of the Survey of Activities and Fear of Falling (SAFFE-C) [46]. The SAFFE-C is a self-reported inventory designed to measure the restriction on respondents’ activity created by FoF. The SAFFE-C consists of 22 items measuring the extent of individuals’ worry over performing 22 activities representing ADLs, mobility and social activity on a four-point Likert scale (0 = not at all worried, 1 = a little worried, 2 = somewhat worried, and 3 = very worried). The Chinese translation of the SAFFE shows excellent internal consistency (Cronbach’s alpha = .95) [46].

##### Balance

Balance ability will be measured using the Berg Balance Scale (BBS) [47], which is considered a valid measure of functional balance in various populations, such as stroke survivors and healthy older adults [48]. The BBS consists of 14 items, each rated on a five-point scale. A score of 41–56 indicates the ability to walk independently, 21–40 indicates the ability to walk with assistance, and 0–20 indicates wheelchair-bound movement.

##### Fall risk

Fall risk will be quantified using the Short-form Physiological Profile Assessment (S-PPA), which consists of five tests: a vision test, a proprioception test, a lower extremity muscle force test, a hand reaction time test, and a balance test [49]. Composite scores are measured on a seven-point scale according to the participants’ responses to the tests. Potential fall risk ranges from −2, representing a very low fall risk, to 4, which represents a very marked fall risk. The S-PPA has been shown to distinguish effectively recurrent fallers from non-fallers among community-dwelling older adults [50].

##### ADL

The respondents’ engagement in ADL will be measured using the Chinese version of the Lawton Instrumental Activities of Daily Living Scale (IADL-C) [51]. The scale’s nine items reflect the respondents’ level of independence in performing nine instrumental ADL: making telephone calls, using transportation, shopping, cooking, housekeeping, undertaking household repairs, doing the laundry, self-medicating, and handling finances.

##### Community reintegration

Community reintegration will be measured using the Chinese version of the Community Integration Measure (CIM-C) [52]. The CIM-C consists of ten items on a five-point scale representing the respondents’ self-reported sense of community reintegration. The CIM has been used for patients with various chronic illnesses, such as acquired brain injury [53] and stroke [52].

##### Health-related quality of life

Quality of life will be assessed using the Chinese version of the Short Form General Health Questionnaire (SF36-C) [54]. The SF36 consists of self-reported items related to physical functioning, role limitations due to physical health problems, bodily pain, general health, vitality, social functioning, and emotional well-being. Two summary scores obtained for a physical component scale (PCS) and a mental component scale (MCS) are converted into a score on a scale from 0 to 100, representing a continuum of disability in which scores of 0 and 100 refer to the maximum and minimum levels of disability, respectively.

### Data analysis

The data will be double-entered to enable validation. Simple descriptive statistics will be used to summarize the sociodemographic characteristics of the participants and other variables of interest. The normality of the data will be examined by a Kolmogorov–Smirnov test. Between-group comparisons at baseline will be performed using *t* tests, Kruskal–Wallis tests, chi-square tests, or Fisher’s exact test, as appropriate.

To measure the changes over time in variables of interest between the two study arms, mixed-effects models with adjustments for potential confounding variables, such as sociodemographic characteristics, will be used. Mixed-effects models go beyond the customary linear framework by incorporating random effects relating to participants. They account well for intra-correlated repeated measures data and accommodate missing data caused by dropouts, as long as the data are missing at random. Pearson and Spearman’s correlation tests, as appropriate, will be used to investigate the correlations between outcome variables. SPSS 17.0 will be used for the remaining statistical analysis, with a 5% level of confidence (two-sided) accepted for significance.

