### Randomization and blinding

Figure 2 presents an overview of the study. After explaining the study’s objectives and obtaining written informed consent, a research assistant will perform a baseline assessment for all of the outcome measures. An offsite volunteer not involved in the recruitment, intervention, or data collection will randomly allocate the participants to either the experimental group or control group in a 1:1 ratio, using the computer program Minimise [36]. The randomization will be stratified based on age (55–70 years or 71–85 years), gender (male or female), and level of subjective balance confidence based on ABC-C scores (< 50 or 50–80) [37]. The participants will be informed of the results of the group allocation and their resulting training schedule and venue by centralized telephone calls from an offsite volunteer to ensure concealed randomization.

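### Allocation is minimised on baseline ABC-C, but the analysis model does not commit to it as a covariate; on the likeliest reading this gives up some precision that is free to recover

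*Protocol article*

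**What the plan says.** **Allocation** (Protocol article, Randomization and blinding). Participants go to the "experimental group or control group in a 1:1 ratio", and the allocation is made "using the computer program Minimise". The first two balancing factors are age band and gender: "stratified based on age (55–70 years or 71–85 years), gender (male or female". The third is the baseline score on the primary outcome scale, split into two bands: "level of subjective balance confidence based on ABC-C scores (< 50 or 50–80".

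**Outcome and visits** (Primary outcome measure; Measurements). The primary outcome is the ABC-C score. There are five measurement occasions, and the first is baseline.

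**Analysis** (Data analysis). The purpose of the model is stated as "To measure the changes over time in variables of interest between the two study arms". The covariate rule that follows is: "mixed-effects models with adjustments for potential confounding variables, such as sociodemographic characteristics, will be used". The model has participant random effects. The balancing factors are not mentioned, and no way of using the baseline value of an outcome is stated. The preceding paragraph of the same section says: "Between-group comparisons at baseline will be performed using" a set of significance tests.

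**The concern.** In a randomised trial, covariates earn their place because they were used in the allocation or because they predict the outcome. The Data analysis section applies a different rule, potential confounding, and illustrates it with a class of variables to which ABC-C does not belong. The protocol therefore balances the arms on the baseline value of its own primary outcome and then does not commit to using that value as a covariate.

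Two things are at stake, both modest. The first is precision: a change-score contrast is generally less efficient than a baseline-adjusted one. The second is the match between the interval and the design: when allocation has balanced a prognostic factor, a model that does not condition fully on it reports a standard error larger than the true sampling spread.

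**Working it through.** The plan gives no figure on this point to reproduce, so the check compares the likely reading of the model with the alternative.

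**1. Inputs.** From the protocol: the three balancing factors, 1:1 allocation, five occasions including baseline, and 76 participants before dropout. Assumed, because the documents do not give them: a baseline to follow-up correlation ρ of 0.5 to 0.8, equal variance at baseline and follow-up, and a minimisation probability of 0.8 or 1.0.

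**2. What the likely model estimates.** If all five occasions are responses and the arm effect is an arm-by-visit term, then with complete data the contrast is the difference between arms in mean change from baseline. Covariates that do not vary over time cancel out of a within-participant change. In a simulated complete data set (76 participants, five visits, random intercept), adding age and sex as main effects left the contrast at 0.1585 and its standard error at 0.1944, both unchanged. By the same argument, adding ABC-C as one more main effect would not help while baseline remains a response. How baseline enters is what matters.

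**3. Variance of the contrast for one follow-up visit**, relative to the outcome variance:

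- change score: 2(1 − ρ)
- baseline-adjusted: 1 − ρ² = (1 − ρ)(1 + ρ)
- change score over adjusted: 2/(1 + ρ)

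| ρ | Change score | Adjusted | Variance ratio | SE ratio |
|---|---|---|---|---|
| 0.5 | 1.00 | 0.75 | 1.33 | 1.15 |
| 0.7 | 0.60 | 0.51 | 1.18 | 1.08 |
| 0.8 | 0.40 | 0.36 | 1.11 | 1.05 |

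**4. Check under minimisation.** The simulation used 76 participants, minimisation on the three factors, no treatment effect, age and sex unrelated to outcome, and 3000 runs per setting. Both analyses adjusted for age and sex. Ranges cover the two minimisation probabilities, and the Monte Carlo error on the type I error is about ±0.008.

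| ρ | Model SE, change | Model SE, adjusted | Ratio | Type I error, change | Type I error, adjusted |
|---|---|---|---|---|---|
| 0.5 | 0.230 | 0.199 | 1.16 | 0.035–0.040 | 0.051–0.053 |
| 0.7 | 0.178 | 0.164 | 1.09 | 0.039–0.044 | 0.047–0.050 |
| 0.8 | 0.145 | 0.138 | 1.05 | 0.045–0.049 | 0.057 |

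The reported standard errors agree with the formula.

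**5. Where the loss shows.** Minimisation already removes part of the baseline imbalance, so the estimates themselves differ less in spread than the reported standard errors do. At ρ = 0.5 with probability 0.8, the empirical standard errors were 0.217 and 0.201, a ratio of 1.08. At ρ = 0.8 they were 0.144 and 0.141, a ratio of 1.02. The rest of the 5–16% is an interval wider than it needs to be, which is the conservatism seen in the type I error.

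**The case against.** The strongest reply is that the sentence is open-ended. It gives an example of covariates, not a closed list, and a journal article may leave the list to an analysis plan that is not shown here. That stands as far as it goes: the document does not exclude ABC-C, and a reader who infers exclusion goes beyond the text. Age and gender are ordinarily counted as sociodemographic, so the gap concerns ABC-C. What remains is that the article states a selection principle, and that principle does not lead to the allocation factor that matters most.

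A second reply is that baseline, as the first of five responses, already contributes much of its information, and that both contrasts are valid under randomisation. This also stands. It is why the loss is 5–16% of the standard error and why the point is an improvement, not the correction of an error.

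Three stronger readings are tempting and lack support:

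- **Covariates will be chosen by baseline p values.** The tests and the model appear in consecutive paragraphs, but no sentence links them.
- **Baseline ABC-C is ignored altogether**, with only post-treatment scores compared. The stated target is change over time, so this is not clearly what is planned.
- **The trial is already short of power, so the loss bites harder.** The sample size of 76 does not follow from the stated inputs alone, but it is not shown to be wrong. A repeated-measures calculation with effect size f = 0.26, four measurements and a correlation of 0.5 returns exactly 76, although those settings are not stated.

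**Conclusion.** The point holds in a limited form. The plan does not commit to baseline ABC-C as a covariate, although allocation is minimised on it and the primary outcome is measured on the same scale. If baseline is used only as a repeated response, the primary contrast has 1.11 to 1.33 times the variance of a baseline-adjusted contrast (reported standard error about 5–16% wider). The two-sided 5% test then runs at about 0.035–0.049. The direction is conservative, so there is no added risk of a false positive.

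The size rests on the assumed correlation of 0.5 to 0.8 and on equal variances. With baseline SD s₀ and follow-up SD s₁, the excess variance is (s₀ − ρs₁)². It vanishes when s₀ = ρs₁, so the loss could be smaller if restricting entry to ABC-C scores below 80 narrows the baseline spread. The formula covers one follow-up visit. For secondary outcomes, the value of adding ABC-C depends on how well it predicts them, which the documents do not say.

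**What to change.** In Data analysis, replace the open-ended reference to potential confounders with a fixed covariate set for every outcome: age, gender, continuous baseline ABC-C, and the baseline value of the outcome analysed (for the primary outcome the last two coincide). State how baseline enters: either as a covariate with only post-baseline visits as responses, or through a mixed model that constrains the arms to a common baseline mean. Adding ABC-C as a main effect while keeping baseline as an unconstrained response would not recover the loss. Present baseline characteristics by arm descriptively, without significance tests.

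The cost is a few sentences of analysis text, best fixed before unblinded data are seen. All the variables are already collected before allocation, so no visit, measure or participant is added.

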### Therapists and research personnel

Two research assistants with at least 2 years of research experience in physical exercise training will be the assessors of this study. They will be given a 1-day training session on obtaining outcome measurements by an experienced physiotherapist before the study. Training will be provided in both the theory and practice of using the outcome measures. All of the assessors will rehearse the outcome measures with the research team personnel to standardize the assessment. To establish the interrater reliability, the two assessors will rate five participants and then review for discrepancies, if any.

The two TOBT therapists will have been trained by an experienced physiotherapist and have at least 2 years of post-qualification experience as therapists in physical exercise training. They will be provided with written progression guidelines (Table 1). A regular review of training records and spot observations will be conducted by the experienced physiotherapist to enhance adherence to the written progression guidelines. The CBT therapists will be three psychiatric nurses who have qualified as cognitive therapists. They will all have at least 5 years of post-qualification experience with applying CBT clinically. A treatment manual and materials have already been developed with reference to Tennstedt et al.’s [13] and Zijlstra et al.’s [14] research on FoF as experienced by community-dwelling older adults and reviewed by the three certified cognitive therapists involved in the study. To ensure treatment integrity, the CBT intervention has already been piloted and audiotaped. Each CBT therapist evaluated the pilot sessions to assess their compliance with the treatment manual, the achievement of session goals, and the use of CBT techniques. The GHE intervention will be delivered by two research assistants not involved in the assessment or any other part of the intervention, using audio-visual aids and materials that have already been developed.

**Table 1 Tab1:** Progression criteria for task-oriented balance training

Exercise	Progression criteria	Method of progression
Stepping up and down	Able to complete 50 times	Starting with a 2-in.-high wooden step, then progressing to 4- and 6-in.-high wooden steps after the progression criteria have been met

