**Fig. 2 Fig2:**
[figure not shown]
Flow diagram for clinical trial

To maintain assessor blinding, the assessment, data entry, and data analysis will all be performed by another full-time research assistant blind to group allocation and not involved in delivering the interventions. The intervention and assessment will be physically separate, performed at different sites. The subjects will be reminded not to disclose any information on their intervention groups to the assessors. However, it will be impossible to blind the therapists and participants to the group allocation.

All of the participants will be asked to undertake 16 sessions of training over an 8-week period. The participants in both groups will undergo 45-min sessions of TOBT in groups of three to five. TOBT is a rehabilitation strategy designed to improve muscle strength in lower limbs and to correct for balance deficits on the paretic side of patients with stroke [30, 38, 39]. Improved strength and balance are gained through the repetition of task-specific functional movements.

The TOBT intervention will consist of five exercises targeting muscle strength in the lower limbs and walking performance: (i) stepping up and down in different directions to strengthen the affected leg muscles and to increase control over shifts in the center of gravity, (ii) heel-raising exercises to strengthen the ankle plantar flexors, (iii) semi-squatting to improve lower limb strength and proprioception in the knees and ankles, (iv) standing on a duraDisc to promote static balance, and (v) walking across a surface covered with obstacles to improve dynamic walking balance.

Based on our practical experience of using TOBT in previous studies of patients with chronic stroke [30, 40], the proposed frequency and intensity of treatment will be effective and tolerable, providing sufficient stimulation to enhance motor recovery in patients with stroke. In the TOBT sessions, the participants will take turns in carrying out one of the TOBT exercises for 8 min, followed by a 1-min rest interval, until the five TOBT exercises have been completed. All the TOBT sessions will be held in the morning, and then the participants attend either the CBT or GHE session on the same day in the afternoon after a 2-hour lunch break.

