#### Experimental group

The experimental group will receive twice weekly CBT sessions for 8 weeks, lasting for 45 min per session, in groups of three to five. The CBT sessions will be focused on eliminating cognitive and behavioral factors known to generate and aggravate impaired subjective balance confidence and fear-avoidance behavior. The aim will be to increase the self-perception of efficacy regarding falls and the sense of control over falling, to decrease the perception of risk, and to help the participants adopt realistic expectations of the consequences of falls. Each week will have a specific theme in the CBT protocol. The main themes and content are summarized in Table 2.

**Table 2 Tab2:** Weekly themes and main content of CBT sessions

Week	Weekly theme
1	Introduction and briefing on the aims of the rehabilitation program • Introduction to group • Introduction of the concept of self-efficacy • Information on post-stroke balance self-efficacy and rehabilitation
2	Understanding the relationships between thoughts, emotions, and behavior • Introduction to the CBT model • Understanding fear, fear of falling, fall risks, and actual falls • Understanding the automatic thoughts and emotional and behavioral reflection associated with fear of falling
3	Exploring thoughts and maladaptive responses • Identifying maladaptive thoughts leading to physical inactivity • Adapting realistic views of fall risk and the consequences of falls • Recognizing risky behavior • Overcoming barriers to physical activity
4	Exploring adaptive thoughts and behavioral responses • Fall prevention strategies and safety issues • Recognizing and minimizing fall risk
5	Implementing and reviewing behavioral changes related to ADL • Setting personal goals for ADL • Planning to achieve personal goals in small stages • Recognizing potential hazards and planning for safety
6	Implementing and reviewing behavioral changes related to social activities • Setting personal goals for social activities • Planning to achieve personal goals in small stages • Recognizing potential hazards and planning for safety
7	Reviewing and advancing individual therapeutic goals • Reviewing personal goals for ADL and social activities • Establishing a regular exercise plan

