8	Consolidating the experiences of the rehabilitation program • Sharing attitudes and experiences of fear of falling before and after the group • Sharing experiences of applying cognitive-restructuring skills • Establishing the long-term personal goals of regular exercise, ADL independence, and social engagement

*ADL* activities of daily living, *CBT* cognitive behavioral therapy

Weeks 1 and 2 of the CBT sessions will focus on introducing the CBT framework and showing how self-perceived capability and maladaptive thoughts can influence behavioral performance. From week 3 to week 8, two major techniques, cognitive restructuring and behavioral modification, will be used in the CBT sessions to achieve participants’ personal goals. Cognitive restructuring attains thought alteration in the following four steps: (1) identification of automatic thoughts, (2) examination of cognitive distortion originating from automatic thoughts, (3) disputing the cognitive distortion and automatic thoughts, and (4) developing adaptive beliefs. In the proposed study, these four steps will be undertaken in the form of CBT homework assignments and sharing and discussion during CBT group sessions.

After effecting cognitive restructuring, the CBT group sessions will target behavioral modification, another crucial component of the intervention. The participants will be equipped to identify potential risks and develop behavioral strategies to prepare them to increase their activity levels safely. The CBT sessions will also serve as a platform for vicarious learning, social persuasion, and social modeling for the participants through group discussion and observing the success of others. In addition, mastery experiences can be gained through the successful application of CBT in daily situations. Indeed, according to Bandura [41], this is the major source of self-efficacy. Therefore, the use of cognitive-restructuring and behavioral-modification techniques is expected to enhance the participants’ subjective balance confidence and reduce their fear-related avoidance behavior.

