#### Control group

The control group will attend 16 health talks (two sessions per week for 45 min per session) delivered as an inactive attention placebo by a research assistant in groups of three to five. The materials used in the GHE sessions will include audio-visual presentations, demonstrations, video clips, mini-games, oral quizzes, and posters and pamphlets on various health topics. The GHE sessions will be designed to raise awareness of general health issues and increase general health knowledge among an elderly population. The details of the GHE sessions are summarized in Table 3.

**Table 3 Tab3:** Weekly topics of general health education sessions

Week	Topic	Content	Materials
1	Home safety	Strategies for removing potential home hazards to prevent residential accidents, such as the proper placement of sharp objects, the safe use of electric appliances, and fire safety.	• Audio-visual presentation • Pamphlets • Video clips
2	Choice of healthy foods	Information on food labels and allergies will be provided to facilitate the choice of healthy foods.	• Audio-visual presentation • Poster • Pamphlets • Mini-games • Oral quiz
3	Diet	Tips on healthy diet, such as a food pyramid and healthy recipes, will be introduced to establish a healthy eating style.	• Audio-visual presentation • Pamphlets • Oral quiz
4	Brain health	Concepts of the mind and memory will be introduced and mini-games relating to brain health will be played to raise awareness of the importance of maintaining brain health.	• Audio-visual presentation • Mini-games • Video clips
5	Hand care	The importance of hand and wrist care will be emphasized and the appropriate choice and use of hand-care products introduced.	• Audio-visual presentation • Demonstration
6	Foot care	The importance of foot and ankle care will be introduced, followed by information on maintaining foot and ankle care.	• Audio-visual presentation • Video clips
7	Flu prevention	Health information, including the symptoms, prevention, and treatment of flu, will be provided and ways to prevent flu discussed.	• Audio-visual presentation • Pamphlets
8	Handicrafts	The importance of developing hobbies and leisure activities will be discussed, followed by a demonstration of some common handicrafts.	• Audio-visual presentation • Demonstration • Mini-games

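### CBT and GHE are given in small groups nested within arm, but the model names only participant random effects; if outcomes correlate within groups, the nominal 5% test is too liberal

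*Protocol article*

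**What the plan says.** Allocation is by individual, 1:1 (Protocol article, Randomization and blinding). Treatment is then given in groups:

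- **CBT** (Experimental group): twice weekly for eight weeks, "lasting for 45 min per session, in groups of three to five".
- **GHE** (Control group): 16 talks, "delivered as an inactive attention placebo by a research assistant in groups of three to five".
- **TOBT** (text after Fig. 2): "The participants in both groups will undergo 45-min sessions of TOBT in groups of three to five". Whether a TOBT group holds one arm or both is not said.

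The Experimental group section makes interaction between members part of how CBT works: "The CBT sessions will also serve as a platform for vicarious learning, social persuasion, and social modeling for the participants through group discussion". On delivery, the section on therapists and research personnel says: "The CBT therapists will be three psychiatric nurses who have qualified as cognitive therapists". Two research assistants deliver GHE.

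Data analysis specifies mixed-effects models "by incorporating random effects relating to participants", justified by repeated measurements and dropout, and tests "with a 5% level of confidence (two-sided) accepted for significance". No group or therapist effect is named. The Sample size section arrives at 76 evaluable participants (38 per arm) and 88 recruited, without an ICC or a design effect.

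**The concern.** A participant random effect accounts for correlation between repeated measurements on one person. It does not account for correlation between different people who attend the same group. Every CBT group lies wholly in one arm and every GHE group wholly in the other, so any group-level variation goes straight into the arm contrast and does not cancel.

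The primary outcome, balance confidence, is also what the CBT group process is meant to change through members' influence on each other. Treating those members as independent sits badly with that mechanism. At stake are the p value and confidence interval for the primary comparison, and the power that 76 evaluable participants really provide.

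**Working it through.** **Inputs from the protocol.** Group size m = 3 to 5; 38 evaluable and 44 recruited per arm; two-sided 5% test; effect size 0.26; power 80%.

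**Assumed input.** ICC, because none is given. Values of 0.01, 0.05 and 0.10 are shown; at 0 there is no problem.

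**1. The plan's own figure.** The article does not say which test gave 76. One variant reproduces it: the between-arm F test of a repeated-measures ANOVA with f = 0.26, alpha 0.05, two arms, four measurements and correlation 0.5. The last two values are assumptions. The noncentrality is 0.26² × 76 × 4 / (1 + 3 × 0.5) = 8.22, and the power is 80.8%. No clustering term enters.

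**2. Error of a test that ignores arm-nested groups.** The design effect is DE = 1 + (m − 1) × ICC. The true standard error is √DE times the naive one, so the type I error is 2 × [1 − Φ(1.96/√DE)].

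Example, m = 4 and ICC = 0.05: DE = 1 + 3 × 0.05 = 1.15; √DE = 1.072; 1.96/1.072 = 1.828; error 6.8%.

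| ICC | m = 3: DE, error | m = 4: DE, error | m = 5: DE, error |
|---|---|---|---|
| 0.01 | 1.02, 5.2% | 1.03, 5.4% | 1.04, 5.5% |
| 0.05 | 1.10, 6.2% | 1.15, 6.8% | 1.20, 7.4% |
| 0.10 | 1.20, 7.4% | 1.30, 8.6% | 1.40, 9.8% |

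Simulation of an individual-level t test with 40 per arm in groups of four agrees: 5.3%, 6.7% and 8.6%. Analysing group means in the same simulated data returns 4.9-5.1%.

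**3. Clustering in the CBT arm only.** Only one arm's variance is inflated, so the factor is 1 + (m − 1) × ICC / 2. For m = 4 it is 1.075 at ICC 0.05 and 1.15 at 0.10, giving 5.9% and 6.8%. Simulation gives 6.1% and 6.8%.

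**4. Groups that mix the arms evenly, as TOBT groups might.** The group effect then largely cancels from the contrast, and the naive test is conservative: 4.6% at ICC 0.05 in simulation (groups of four, two from each arm).

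**5. Power, under the variant in step 1.** Dividing the noncentrality by DE for groups of four in both arms gives 79.6% at ICC 0.01, 75.1% at 0.05 and 69.9% at 0.10. This keeps 74 denominator degrees of freedom, so it is slightly optimistic.

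**6. Number of groups.** 38/5 = 7.6 and 44/3 = 14.7, so about 8 to 15 groups per arm.

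**The case against.** Four objections carry weight.

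- **The sentence on random effects describes mixed models in general, in a condensed article.** A reader might infer that a group term is ruled out. The text does not say so. But it is the only statement of the random structure, its stated purpose is repeated measurements and dropout, and the sample size carries no clustering allowance either. The point concerns the model as stated.
- **No ICC is given.** A reader might infer that the type I error of this trial does exceed 5%. The documents do not support that as a fact: at an ICC of 0 the error is 5.0%, and at 0.01 the excess is half a percentage point or less. The result is conditional.
- **The stated mechanism is specific to CBT.** GHE is an attention placebo that, under Choice of comparator, is meant to avoid balance confidence, avoidance, falls and physical activity. Equal clustering in both arms may therefore be too pessimistic, and the CBT-only figures are the fairer lower case.
- **Not every group need be nested in arm.** A reader might count all treatment as arm-nested. That holds for CBT and GHE. For TOBT it is unstated, and evenly mixed groups would push the error the other way.

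Two limits apply to the arithmetic. It uses a simple comparison of two arms, not the planned covariate-adjusted repeated-measures model. It also uses full group sizes: 38 evaluable participants in 11 groups average 38/11 = 3.45, for which the error is about 6.4% at ICC 0.05 and 7.9% at 0.10. Both lie inside the range shown.

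**Conclusion.** The point holds conditionally. The CBT and GHE groups are nested in arm, the protocol itself gives a reason to expect correlated outcomes within CBT groups, and neither the stated model nor the sample size allows for it. If the ICC is positive, the standard error of the arm effect is understated, by about 5-10% at ICC 0.05 and 10-18% at 0.10 in relation to the naive value when both arms cluster. The matching type I errors are 6.2-7.4% and 7.4-9.8%. With groups of four and clustering in the CBT arm only, they are about 6% and 6.8%. The ICCs are assumptions, and TOBT groups could add to or offset the effect depending on how they are formed. This is a modest, conditional inflation, best classed as a cheap improvement.

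**What to change.** - Record the CBT or GHE group that each participant attends, and the TOBT group where its membership differs. State how TOBT groups are formed.
- Add to the mixed model a random intercept for therapy group nested in arm. Let its variance differ between arms, or fit it in the CBT arm only as a sensitivity analysis. Use small-sample degrees of freedom, such as Satterthwaite.
- Restate the power of the planned sample over a range of assumed ICCs, such as 0.01 to 0.10. No extra enrolment is asked for.

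The cost is one or two recorded variables and one model term. Intervals become slightly wider, the stated power less favourable, and the group variance rests on only about 8 to 15 groups per arm, so it will be estimated imprecisely.
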